**Sample size**

A pre-randomization survey in the pre-intervention period at participating clusters was conducted. The proportion of AIS patients receiving IVT with DNT ≤ 60 minutes in China was 62%. Based on the outcomes reported by previous studies, a sample size estimation with a change from 55% to 70% of patients with DNT ≤ 60 minutes is clinically important.^10^ Therefore, a total of 1424 patients at 22 hospitals will be required to detect a 15% improvement in AIS patients with DNT ≤ 60 minutes, with 80% power, 5% significance level, and an intracluster correlation coefficient (ICC) of 0.05.

**Statistical Analysis Plan**

We will use the intention-to-treat analysis to analyze all outcomes. The baseline characteristics of hospitals and patients will be analyzed between the PEITEM and control groups. We will summarize continuous variables as median with interquartile ranges and categorical variables as frequency and percentage, and analyze them by using Wilcoxon rank-sum test and Chi-square test separately. Modes will be used to impute missing values of categorical variables, and medians will be imputed for missing values of continuous variables.

Intra-cluster correlation coefficients (ICC) will be calculated using the correlation-based estimation methods for categorical outcomes and analysis of variance methods for continuous variables, respectively.^19^ Generalized estimating equation models with an exchangeable working correlation structure will be conducted to account for the correlations of observations within clusters (hospitals).^20^ Odds ratios for the binary outcomes (DNT ≤ 60 minutes, sICH, favorable functional outcome at 90 days, and death at discharge) and mean differences for the continuous outcomes (DNT, ONT, and mRS score at discharge) will be estimated to assess the treatment effects. Multivariable model for DNT ≤ 60 minutes, DNT, and ONT will be adjusted for patient characteristics (including age, sex, history of stroke/TIA, hypertension, diabetes, atrial fibrillation, coronary heart disease, prior antiplatelet usage, thrombectomy, smoking, prestroke mRS score, and NIHSS score at admission) and hospital characteristics (including hospital grade [tertiary and secondary], stroke unit, teaching hospital status, and annual stroke discharge). Clinical outcomes will be adjusted for age, pre-stroke mRS score, NIHSS score at admission, and other patient characteristics with a p value of <0.1 in the univariate analysis.

Additionally, to assess whether the improvement in primary and secondary outcomes in the PEITEM group is influenced by the time window, we will conduct a sensitivity analysis with the additional inclusion of patients receiving IVT beyond 4.5 hours upon stroke onset. All patients receiving IVT beyond 4.5 hours upon stroke onset should have CT or MRI core/perfusion mismatch. For patients lost to follow-up at 90 days, we will use multiple imputation as a sensitivity analysis and compared the baseline characteristics between patients with and without mRS at 90 days. A two-tailed P < 0.05 is considered statistically significant. All analyses will be performed using SAS (version 9.4) and R software (version 4.0.5). As no detrimental problems to the participant are anticipated, there are no formal stopping rules for the trial. This trial is registered with ClinicalTrials.gov, number NCT03317639.

**Fig A** Study design and timeframe.

**
[figure not shown]
**

**Fig B** A PEITEM intervention diagram and its relationship with the BCW methods.

[figure not shown]

Abbreviations: BCW, Behaviour Change Wheel; DNT, Door-to-Needle Time.

**Table A** Description of PEITEM Intervention according to the Behavior Change Wheel Components.

| Intervention | Definition | Activity |
| --- | --- | --- |
| **P**ersuasion | Using communication to induce positive or negative feelings or stimulate action | 1. Monthly video teleconference between stroke doctors from PEITEM hospitals and research team for face-to-face problem solving; 2. Monthly DNT feedback by setting up DNT target, time tracking with feedback, discussion about the reasons of delay and improving measures through case discussion. |
| **E**nvironment Reconstruction | Changing the physical or social context | Implementation of standardized medical record templates involving evidence-based performance measures in the electronic medical record. |
| **I**ncentivization | Creating expectation of reward | Establishment of a pioneer award of IVT to the hospitals according to the number of IVT patients and the proportion of DNT ≤60min by research team. |
| **T**raining | Imparting skills | Training of sustainable application of quality improvement tools to help hospitals to establish their own personalized, efficient and stable code stroke workflow via video teleconference. |
| **E**ducation | Increasing knowledge or understanding | Education involving early identification of eligible patients for IVT, and rapid decision-making based on rapid risk evaluation of hemorrhagic transformation and complication management such as hypertension and hyperglycemia via video teleconference. |
| **M**odeling | Providing an example for people to aspire or imitate | Championship experience presentation by the PEITEM hospital with shortest DNT via video teleconference monthly. |

Abbreviations: DNT, Door-to-Needle Time; IVT, Intravenous thrombolysis.

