**Clusters randomization and blinding**

Because the hospitals are the intervention targets, they are used as the randomization unit to minimize contamination. The hospitals will be stratifically randomized with a 1:1 allocation ratio according to their baseline proportion of IVT patients with DNT ≤60 minutes (<60%, ≥ 60% -≤ 72%, >72%) collected in the pre-intervention period. The randomization will be conducted by using a computer generated randomisation sequence, by which eleven hospitals are assigned to the intervention group and another eleven hospitals to the control group. Masking the hospital personnel and clinical investigators to site or group assignment is not possible because of the intervention nature. Nevertheless, external clinical evaluators assigned to assess the outcomes will be masked.

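### Patient baseline characteristics are compared between arms with tests that ignore clustering by hospital, and covariates for the clinical outcomes are chosen by an undefined p<0.1 screen

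*Protocol*

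**What the plan says.** The section on cluster randomisation makes the hospital the unit: "Because the hospitals are the intervention targets, they are used as the randomization unit to minimize contamination", and "eleven hospitals are assigned to the intervention group and another eleven hospitals to the control group". The Sample size section allows for clustering with "an intracluster correlation coefficient (ICC) of 0.05".

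The Statistical Analysis Plan section then states: "The baseline characteristics of hospitals and patients will be analyzed between the PEITEM and control groups". Continuous and categorical variables are summarised, and the plan will "analyze them by using Wilcoxon rank-sum test and Chi-square test separately". No allowance for hospital is stated for these tests. The next paragraph specifies generalised estimating equations (GEE) with an exchangeable working correlation by hospital for the outcomes.

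The same paragraph treats covariates in two ways. DNT ≤ 60 minutes, DNT and ONT have a fixed list of patient and hospital characteristics. Clinical outcomes are adjusted for age, prestroke mRS, admission NIHSS and "other patient characteristics with a p value of <0.1 in the univariate analysis". The protocol does not say whether that univariate analysis relates a characteristic to the outcome or compares it between arms, or whether it allows for clustering.

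**The concern.** The Wilcoxon rank-sum and chi-square tests assume independent observations. Arm is constant within a hospital, so any hospital-to-hospital variation in case mix goes straight into the between-arm difference, and the naive standard error leaves it out. The plan recognises this for outcomes but not for patient characteristics.

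The baseline table matters more here than in an individually randomised trial. Patients enter after their hospital has been allocated, the trial is open label, and the intervention works on who receives thrombolysis: it trains staff to recognise eligible patients early, aims to reduce refusal, and rewards the number treated. Readers will therefore look to the table for differential selection. P-values that are too small cannot separate such selection from ordinary variation between hospitals.

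The second issue is the covariate rule for clinical outcomes. A p<0.1 screen lets the data choose the adjustment set, and its definition is left open.

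**Working it through.** **Inputs from the protocol.** "a total of 1424 patients at 22 hospitals will be required to detect a 15% improvement"; eleven hospitals per arm; ICC 0.05 for the sample size; 55% versus 70%; 80% power; two-sided 5%.

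**Assumed.** The ICC of patient characteristics, taken as 0.01 to 0.05, and the variation in hospital size, expressed as a coefficient of variation (CV). The protocol gives neither.

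**The plan's own figure.** Mean hospital size m = 1424/22 = 64.7. Design effect at ICC 0.05 = 1 + 63.7 × 0.05 = 4.19. Effective sample size per arm = 712/4.19 ≈ 170. Power for 55% versus 70% is then 81.8% (about 78.5% with a t reference on 20 degrees of freedom). The stated size is consistent with the stated ICC, so clustering was allowed for at the design stage.

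**Naive between-arm tests.** With design effect DE, the true false-positive rate is 2 × [1 − Φ(z/√DE)], where z = 1.96 for a 5% test and 1.645 for a 10% test. The null is that case mix does not depend on arm. With equal hospital sizes, DE = 1 + 63.7 × ICC:

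| Assumed ICC | DE | Nominal 5% | Nominal 10% |
| --- | --- | --- | --- |
| 0.01 | 1.64 | 12.6% | 19.9% |
| 0.02 | 2.27 | 19.4% | 27.5% |
| 0.05 | 4.19 | 33.8% | 42.1% |

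Simulation with 22 near-equal hospitals (4000 runs per setting) agrees. At ICC 0.01 it gave 12.8% (chi-square) and 12.2% (Wilcoxon); at ICC 0.05 it gave 33.4% and 33.5%.

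**Unequal hospital sizes.** DE = 1 + [(1 + CV²)m − 1] × ICC. At ICC 0.05 and CV 0.5, DE = 5.00 and the formula gives 38.1% (simulation about 37%). At CV about 0.6, simulation gave 39% (chi-square) and 38% (Wilcoxon). So about 37–39% at ICC 0.05 if sizes vary this much.

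**Expected false flags.** The fixed list names 12 patient characteristics. If all were tabulated, the expected number flagged at 5% with equal sizes is 12 × 0.126 = 1.5 at ICC 0.01 and 12 × 0.338 = 4.1 at ICC 0.05, against 12 × 0.05 = 0.6 for a valid test.

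**The p<0.1 screen, two readings.** Three of the 12 characteristics are forced in, so nine could be screened.

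- *Between-arm comparison.* The last column of the table applies: a null characteristic is selected about 20% to 42% of the time instead of 10%.
- *Association with the outcome.* The characteristic varies within hospital, so the naive design effect is about 1 + 63.7 × ICC(covariate) × ICC(outcome). With both at 0.05 (assumed), it is 1 + 63.7 × 0.0025 = 1.16, and the null selection rate is 2 × [1 − Φ(1.645/√1.16)] ≈ 12.7% (simulation 12.9%). With a covariate ICC of 0.01, it is 1 + 63.7 × 0.0005 = 1.03 and about 10.5%.

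**The case against.** The strongest reply is that the baseline tests are descriptive and feed nothing that counts. The models for DNT ≤ 60 minutes, DNT and ONT have a fixed covariate list, and GEE handles clustering for the outcomes. This stands, and it limits the point to reporting and to the clinical-outcome models.

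A reader might infer that the naive tests decide which covariates enter the clinical models, because they are the only univariate tests the protocol names. The text does not establish this. The screen is described beside the multivariable outcome models, in a different paragraph from the baseline tests, and the more natural reading is a covariate-outcome association, possibly through the same GEE. On that reading the screen stays close to its nominal 10% even if clustering is ignored. A separate SAP may also define the term. What remains is that the adjustment set is data-driven on either reading.

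It is also fair to say that the ICC of 0.05 belongs to a hospital process measure and need not apply to age or diabetes. The rates are therefore conditional, although even ICC 0.01 gives about 2.5 times the nominal 5%.

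Finally, not every flagged difference would be an artefact. Because patients enter after open-label allocation, some could reflect real selection, so a valid formal check may be worth keeping. For hospital-level characteristics the hospital is the observation, and the tests raise no clustering problem.

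**Conclusion.** The point holds for patient-level characteristics: the stated tests do not match the unit of randomisation and give p-values that are too small. The false-positive rate at a nominal 5% is about 13%, 19% and 34% for assumed ICCs of 0.01, 0.02 and 0.05 with equal hospital sizes, and about 37–39% at ICC 0.05 if sizes vary with a CV of about 0.5–0.6. None of these rates can be read as established for this trial, because the protocol gives neither an ICC for patient characteristics nor the spread of hospital sizes.

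The covariate screen is a separate and smaller matter. It needs a definition, and its null selection rate is about 20–42% on one reading and about 10–13% on the more natural one. Either way, the same section fixes covariates in advance for the time outcomes but lets the data choose for the clinical ones.

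The impact is small, and nothing here calls the primary result into question.

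**What to change.** For patient characteristics, report summaries by arm with standardised differences and no p-values. If a formal check for selection after randomisation is wanted, use tests that respect the hospital: comparisons of hospital-level summaries, or GEE with a small-sample correction for 22 clusters. Tests on hospital-level characteristics can stay.

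For the clinical outcomes, replace the p<0.1 screen with a fixed list: age, prestroke mRS, admission NIHSS and any others named in advance. If the screen is kept, state whether it tests association with the outcome or difference between arms, and whether it allows for clustering.

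The cost is a few lines of text and a changed table; no new data are needed. What is given up is the familiar baseline p-values and the freedom to let the data choose covariates.

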**Outcomes**

The primary outcome is the proportion of DNT ≤ 60 min in the AIS treated with IVT, indicating a fast thrombolytic treatment from hospital arrival. The secondary outcomes include the key time intervals between assessment and thrombolytic treatment (median DNT, ONT), mRS score and death at discharge, complications after IVT [symptomatic intracranial hemorrhage (sICH)] and favorable functional outcomes (score of 0 to 1 on the mRS at 90 days), which indicate the efficiency and safety of PEITEM intervention. The DNT is defined as the time between hospital arrival and the initiation of IVT. The ONT is defined as the time between the symptom onset and the initiation of IVT. sICH is defined as intracranial hemorrhage at 24 hours associated with an increase of ≥4 points of NIHSS score from baseline, according to European Cooperative Acute Stroke Study (ECASS) II trial.^18^

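### The mode/median rule for missing values is not limited to baseline covariates, so as written it also fills in missing outcomes, including the primary one

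*Protocol*

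**What the plan says.** The first paragraph of the Statistical Analysis Plan section opens with "We will use the intention-to-treat analysis to analyze all outcomes". It continues with "The baseline characteristics of hospitals and patients will be analyzed between the PEITEM and control groups", describes summary statistics and two-group tests, and ends with the rule "Modes will be used to impute missing values of categorical variables, and medians will be imputed for missing values of continuous variables". The rule neither names covariates nor excludes outcomes. It also does not say whether the mode or median is taken overall, by arm or by hospital.

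The next paragraph sorts the outcomes into the same two types. One group is "Odds ratios for the binary outcomes (DNT ≤ 60 minutes, sICH, favorable functional outcome at 90 days, and death at discharge"; the other is "mean differences for the continuous outcomes (DNT, ONT, and mRS score at discharge". The Outcomes section makes the first of these the primary endpoint: "The primary outcome is the proportion of DNT ≤ 60 min in the AIS treated with IVT".

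The only other statement on missing data comes later in the same section: "For patients lost to follow-up at 90 days, we will use multiple imputation as a sensitivity analysis", with a baseline comparison of patients who do and do not have a 90-day mRS. Nothing separate is said about missing DNT, ONT, sICH or death.

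**The concern.** Filling an outcome with its most frequent value is not neutral. Every patient with a missing primary outcome would be given the same result, and the model would treat that result as observed. Proportions move toward the commoner category and standard errors come out too small. If the arms differ in how much is missing, the filling alone produces a difference between them.

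For the safety outcomes, a patient who was not assessed would be counted as free of the event. The primary endpoint is a binary process measure whose planned rates lie above 50% in both arms, so the filled value would be a success in both.

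**Working it through.** The plan gives no missing-data figure, so there is none to reproduce. The inputs from the Sample size section are 62% with DNT ≤ 60 min before the intervention, planning rates of 55% and 70%, and 1424 patients (712 per arm at 1:1). **All missing shares below are assumptions**, with values missing completely at random within arm.

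**1. Which value is filled in.** At 55%, 62% or 70% the mode of the binary outcome is DNT ≤ 60 min. More than half of patients are at or below 60 min, so the median DNT is also at most 60 min. Filling the indicator directly, or filling DNT and then dichotomising, gives a success either way (mode or median taken overall or by arm).

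**2. Equal missingness.** With true proportion p and missing share d, the filled proportion is p(1 − d) + d. The risk difference is multiplied by (1 − d).

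| d in both arms | Control (true 55%) | PEITEM (true 70%) | Difference | OR (true 1.91) |
|---|---|---|---|---|
| 2% | 55.9% | 70.6% | 14.7 | 1.89 |
| 5% | 57.3% | 71.5% | 14.3 | 1.87 |
| 10% | 59.5% | 73.0% | 13.5 | 1.84 |
| 20% | 64.0% | 76.0% | 12.0 | 1.78 |

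**3. Unequal missingness, no true effect (62% in both arms).**
- Control 10%, PEITEM 3%: 0.62 × 0.90 + 0.10 = 65.8% and 0.62 × 0.97 + 0.03 = 63.1%. That is −2.7 points, OR 0.89.
- The reverse gives +2.7 points.
- Control 10%, PEITEM 5%: 65.8% and 63.9%, or −1.9 points. The reverse gives +1.9.

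**4. Unequal missingness, true 55% versus 70%.** Control 10%, PEITEM 3%: 59.5% and 0.70 × 0.97 + 0.03 = 70.9%. The difference is 11.4 points instead of 15.0.

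**5. Precision.** With 712 per arm and ignoring clustering, the standard error from the filled data is 0.965, 0.928 and 0.850 of the complete-case standard error at 5%, 10% and 20% missing. Part of this is the false gain in sample size, and part is the shift of the proportions away from 50%.

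**6. 90-day mRS 0–1 (rates assumed).** With 40% versus 45% and 10% missing, the filled value is 'no' and the result is 36.0% versus 40.5%. With 48% versus 53% and 10% missing, an overall mode gives 53.2% versus 57.7% (4.5 points). A mode taken by arm gives 0.48 × 0.90 = 43.2% versus 0.53 × 0.90 + 0.10 = 57.7% (14.5 points). The protocol does not say which is meant.

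**7. sICH and death.** If the event affects fewer than half of patients, the filled value is 'no event' and a true rate r becomes r(1 − d).

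**The case against.** A reader might infer that the protocol commits to mode filling as the main analysis of every outcome. The text does not establish that. The rule closes a paragraph largely about baseline description and uses the usual terms of such a paragraph. Outcome modelling begins in the next paragraph, and its models need about a dozen patient covariates, so a simple covariate fill has an obvious purpose. For 90-day mRS, multiple imputation as a sensitivity analysis, paired with a comparison of patients with and without the score, fits a complete-case main analysis.

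A reader might also infer that missing DNT will be common and uneven between arms. The documents give little support for this. Eligibility requires IVT within 4.5 hours, so onset and needle times should be known, and DNT would be missing mainly when the arrival time is missing. Both arms use the same web-based entry with logic checks, independent data entry, CRO checks of recruitment and quarterly record review. Monthly feedback and record templates in PEITEM hospitals could still affect completeness there, but the 10% versus 3% split is only an illustration.

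These arguments limit the likely size and the certainty about intent. They do not settle the scope. The paragraph starts from the analysis of all outcomes, and the ICC sentence that follows uses the term continuous variables for quantities that include outcomes. On the covariate-only reading, the protocol names no main-analysis handling of missing 90-day mRS.

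**Conclusion.** The point holds as a defect in a stated rule: its scope is open, and read literally it fills in outcomes, the primary one included. Multiple imputation does not cure this, since it never touches DNT and is only a sensitivity analysis at 90 days.

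The size rests entirely on assumed missingness. Equal missingness of 2% to 10% pulls a true 15.0-point difference down to between 14.7 and 13.5 points. Unequal missingness of 10% versus 3% creates 2.7 points in either direction when there is no effect. If DNT is nearly complete, as the data checks make plausible, the effect on the primary result is small. The 90-day outcome, collected by telephone and with losses expected by the plan itself, is more exposed. If the sponsor intended covariates only, what remains is to say so and to name the main 90-day analysis.

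**What to change.** - State that mode and median filling applies to baseline covariates only, and that DNT, ONT, sICH, death and mRS at any time point are excluded.
- Analyse missing DNT as missing. Add a sensitivity analysis that counts it as > 60 min in both arms. That analysis is not neutral either: with 62% in both arms and 10% versus 3% missing it gives 0.62 × 0.90 = 55.8% and 0.62 × 0.97 = 60.1%, or +4.3 points. It belongs beside the main result, not in its place.
- For 90-day mRS, name a main analysis without mode filling. Either multiple imputation that respects the clustering by hospital, or complete cases with the planned multiple imputation kept as the sensitivity analysis, would do. The exact imputation model is a matter of preference.

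The cost is a change of wording, a little programming and slightly wider intervals. No new data and no change of design are needed.

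### The analysis adjusts for neither the hospital's baseline DNT ≤60 proportion nor the randomisation stratum built on it, which makes the test conservative and wastes power by an amount the protocol's figures cannot settle

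*Protocol*

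**What the plan says.** The section on cluster randomisation states: "The hospitals will be stratifically randomized with a 1:1 allocation ratio according to their baseline proportion of IVT patients with DNT ≤60 minutes". It gives three bands for that proportion, takes the data from the pre-intervention period, and adds that "eleven hospitals are assigned to the intervention group and another eleven hospitals to the control group". The Outcomes section makes the same proportion, measured during the intervention, the primary outcome. The Design section gives both periods the same length, calendar 2018 and calendar 2019.

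The Statistical Analysis Plan section uses generalised estimating equations (GEE) with an exchangeable working correlation. It then describes a multivariable model for DNT ≤60, DNT and ONT with 12 patient characteristics and four "hospital characteristics (including hospital grade [tertiary and secondary], stroke unit, teaching hospital status, and annual stroke discharge"). The baseline proportion and the stratum appear neither there nor elsewhere in the analysis text. The section does not say whether the GEE without covariates or the multivariable one is primary.

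**The concern.** Stratifying makes the arms more alike on baseline performance than simple randomisation would. An analysis that ignores the stratifier still counts the variation it removed as error, so its standard error is too large for the design. The stratifier is also the outcome itself, one year earlier in the same hospitals, and so a natural candidate for explaining differences between hospitals. Those differences dominate precision here. The plan nevertheless names four other hospital-level variables on 22 clusters and leaves this one out. At stake is the power of the primary comparison and whether its nominal 5% level is actually used.

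**Working it through.** **Inputs from the protocol.** Sample size section: "a change from 55% to 70% of patients with DNT ≤ 60 minutes is clinically important"; "a total of 1424 patients at 22 hospitals will be required to detect a 15% improvement"; "with 80% power, 5% significance level, and an intracluster correlation coefficient (ICC) of 0.05". Analysis section: "A two-tailed P < 0.05 is considered statistically significant". Randomisation: 11 hospitals per arm, stratified "according to their baseline proportion of IVT patients with DNT ≤60 minutes (<60%, ≥ 60% -≤ 72%, >72%) collected in the pre-intervention period". Overall baseline proportion: 62%.

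**Assumptions not in the protocol.** r is the correlation of hospital effects between 2018 and 2019. R² is the share of between-hospital variance explained by the four hospital covariates. Each hospital has 65 patients in each year.

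**1. The plan's own figure.** Per arm, n = (1.960 + 0.842)² × (0.55×0.45 + 0.70×0.30) / 0.15² = 159.6, rounded up to 160. With 70 patients per hospital the design effect is 1 + 69×0.05 = 4.45, and 2 × 160 × 4.45 = 1424, as stated. The 70 is inferred, because the protocol gives no cluster size. The point below does not depend on it.

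**2. How much of the error lies between hospitals.** 1424/22 = 64.7 patients per hospital, so the design effect is 1 + 63.7×0.05 = 4.19. The between-hospital share of the variance of a hospital's observed proportion is 0.05 / (0.05 + 0.95/64.7) = 0.05/0.0647 = 0.77.

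**3. Power with no hospital covariates.** SE of the difference = √[(0.2475 + 0.21) × 0.0647 / 11] = 0.0519, and 0.15/0.0519 = 2.89. A t test on 20 degrees of freedom then has about 79% power, close to the planned 80%.

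**4. What the baseline could explain.** The squared correlation between a hospital's two observed proportions is about (0.77 r)²: 0.15, 0.29 and 0.48 at r = 0.5, 0.7 and 0.9.

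**5. Simulation.** 20,000 trials per setting. Binary outcomes in 22 hospitals of 65, randomised within the three stated bands to 11 against 11, were analysed by hospital-level regression with a t reference, standing in for a GEE valid for few clusters. Monte Carlo error is about 0.3 points per power figure. The table shows power with the four covariates → power after adding the baseline log-odds, with the gain in points.

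| R² | r = 0.5 | r = 0.7 | r = 0.9 |
|---|---|---|---|
| 0 | 68% → 73% (+4.7) | 68% → 79% (+11.4) | 69% → 90% (+21.1) |
| 0.2 | +1.3 to +3.5 | +6.6 to +8.5 | +14.8 to +15.6 |
| 0.4 | −1.2 to +2.1 | +2.3 to +5.8 | +8.2 to +9.9 |

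Where a range is given, the first value takes r as the total correlation and the second as the correlation left after the four covariates. At r = 0.3 or 0 the change lies between −2.0 and +0.9 points.

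If the model has no hospital covariates, adding the baseline moves power from 79% to 83%, 79% to 89% and 81% to 96% at r = 0.5, 0.7 and 0.9 (R² = 0).

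**6. Type I error, nominal 5% two-sided.** Ranges are over R² = 0 to 0.4.

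| Model | r = 0.5 | r = 0.7 | r = 0.9 |
|---|---|---|---|
| No hospital covariates | 3.0–4.0% | 2.2–2.9% | 1.4–1.6% |
| Four hospital covariates | 4.3–5.1% | 3.3–4.6% | 2.3–3.7% |

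With the baseline in either model, every setting lies between 4.6% and 5.3%.

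**The case against.** The strongest case on the other side is that nothing here is invalid. The error is on the safe side, with no bias or excess of false positives shown. The benefit rests on two quantities the protocol does not report. If hospital performance is unstable from year to year, or the four covariates already carry most of the prognostic information, the gain is small or nil. The covariate list opens with the word including, and a separate analysis plan may exist. All of this stands, and it limits the severity. It does not remove the point: a list that goes down to smoking and coronary disease but passes over the stratifier reads as a choice, and the stratifier is in neither GEE as described.

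A reader might infer more than the protocol supports:

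- **That the plan loses about 20 points of power.** Replacing the four covariates with the baseline does gain about 21 points if r = 0.7 and the four explain nothing. The protocol supports neither condition, and that comparison combines adding one variable with deleting four. Across plausible settings the swap runs from a loss of up to about 5 points to a gain of about 28.
- **That four hospital covariates exhaust the degrees of freedom.** Going from 20 to 16 costs about 1 point (78.6% to 77.5%). Four useless covariates do cost about 11 points in all, but nearly all of that is chance imbalance between arms. If they explain 40% of between-hospital variance, they raise power instead.
- **That the four are weak predictors, or that stroke unit hardly varies.** Neither is documented. Hospitals with equivalent staffing in place of a stroke unit are eligible, so that variable can vary.

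**Conclusion.** The point holds as an efficiency and design-matching defect that should be fixed. It is not a threat to validity. The stratification variable is absent from the stated analysis. Under a test valid for few clusters, this makes the comparison conservative: about 1.5–4% without hospital covariates for r of 0.5–0.9, and about 2.3–5.1% with the four planned ones, the effect fading as those covariates explain more.

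The power forgone by not adding the baseline to the four covariates is about 5 to 21 points for r of 0.5–0.9 if R² = 0, about 1 to 16 points if R² = 0.2, and between −1 and +10 points if R² = 0.4. At r of 0.3 or less there is little or nothing to gain, and a loss of up to about 2 points is possible.

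No single figure can be claimed, because the protocol gives neither r nor R². The figures also leave out the 12 patient covariates and assume equal hospital sizes. A GEE with an uncorrected sandwich variance would show different nominal power and error rates.

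**What to change.** Add the hospital's pre-randomisation DNT ≤60 proportion, as a continuous log-odds or at minimum as the stratum, to the GEE for DNT ≤60. Name that baseline-adjusted model as the single primary analysis. For DNT and ONT, adjust for the stratifier, or for the hospital's 2018 value of the same measure if it was recorded.

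Keeping the four other hospital covariates is optional. Dropping them helps only if they predict weakly, so that choice should be made and justified before outcome data are analysed. Extending the adjustment to the clinical outcomes is a separate judgement that this point does not settle.

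The cost is a change of wording and one model term (two if the stratum is used). The stratifier had to be known for every hospital in order to randomise. If it turns out not to be prognostic, the price is about 1 to 2 points of power.
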